### Outcomes

Table 1 lists the study’s primary and secondary outcome measures. The primary outcome measures are (1) child dietary diversity measured as the number of food groups out of eight consumed by the child in the preceding day (24 h) [32] and (2) child development, comprising child cognitive, language, motor, and socioemotional development, directly assessed using the Bayley Scales of Infant and Toddler Development, Third Edition (BSID-III), which has been previously adapted and validated for use in Tanzania [33]. Outcomes are assessed on all participating households at baseline and after 6 and 12 months of intervention (detailed in Table 2 per SPIRIT Guidelines).

**Table 1 Tab1:** Primary and secondary outcomes in the EFFECTS trial and timing of assessment

Outcomes	Measures	Baseline	6 months	12 months
Primary outcomes				
Child dietary diversity (24 h)	Number of food groups out of eight food groups consumed in the previous day (24 h) by children aged 6+ months, based on WHO guidelines	x	x	x
Child development	Cognitive, language, motor, and socioemotional development, assessed using the Bayley Scales of Infant and Toddler Development, Third Edition (BSID-III)	x	x	x
Secondary outcomes	Primary, secondary, and process outcomes and measures			
Child dietary diversity (7 days)	Number of food groups out of eight food groups consumed in the previous 7 days by children aged 6+ months, based on WHO guidelines	x	x	x
Child nutritional status	Height-for-age *z*-scores (HAZ) and weight-for-height *z*-scores (WHZ), based on WHO Multicentre Child Growth Standards	x		x
Minimum meal frequency	Proportion of children aged 6+ months (breastfeeding and non-breastfeeding) meeting minimum meal frequency guideline based on the WHO-UNICEF tool	x	x	x
Household allocation of animal source foods	Change in proportion of children (aged 6+ months), mothers, and fathers consuming eggs or meat the previous day given that at least one of the three consumed eggs or meat the previous day	x	x	x
Maternal and paternal infant and young child (IYCF) knowledge and practices	Caregiver knowledge and practice questionnaire regarding age-appropriate infant and young child (1) breastfeeding and support and (2) complementary feeding, measured using an adapted version of the the WHO-UNICEF tool	x	x	x
Responsive feeding practices	Maternal responsive feeding behavior tool	x		x

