**Fig. 2 Fig2:**
[figure not shown]
The EFFECTS process evaluation framework

The EFFECTS process evaluation started with documentation of the training and will continue throughout implementation in the four EFFECTS intervention arms. An overview of the process evaluation data collection tools is presented in Table 3. Depending on the type of process evaluation data, data will be collected by either the CHWs, PCI field supervisors (FS), or two PCI monitoring and evaluation (M&E) officers at specific times during the implementation of the peer group sessions. While the FS are the direct supervisors and mentors of the CHWs, the PCI M&E officers function more independently as they are not directly linked to any specific group of CHWs nor do they provide routine technical (content/behavior change) support to the CHWs. The team of CHWs, FS, and M&E officers is independent of the outcome evaluation team. Data are collected routinely by the CHWs, FS, and M&E officers on tablets with limited paper-based data collection (e.g., pre- and post-training knowledge).

**Table 3 Tab3:** EFFECTS process evaluation data collection tools. *CHWs* community health workers, M*&*E monitoring and evaluation, *PM* project manager

Acronym and form #	Form name	Collected by	Respondent type	Frequency	Framework addressed	Key variables of interest

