**Fidelity—dose received**						
PGA (6)	Peer group attendance register	CHWs	Peer group participants	Beginning of each bi-weekly peer group session	Dose received (structure and quantity)	Participant attendance (male and female); can be used to assess equality of reach but depends on demographic data we collect (Purdue/Harvard will have to do this)
HVLSR (7)	Home visit log and session report	CHWs	Peer group participants	After every home visit is conducted	Dose delivered, dose received (structure/exposure)	For participants who miss group sessions, documents home conducted by CHW, content/messages received during home visits, reasons for missing session, challenges faced by the participant
TERM (8)	Study termination form for participants	CHWs	Peer group participants	If/when a participant drops out of the study	Dose received (quantity and exposure)	ID # of dropped; CHW, date dropped; reason for withdrawal and duration in the study
PGE (9)	Participant group evaluation form	M&E officers	Peer group participants	5% of participants every month	Dose received (exposure and satisfaction); also covers aspects of spillover and community demand	Participant feedback on facilitation and satisfaction (delivery, encouraged to participate openly, topics relevant/important, perception of CHW knowledge, enough time during session, practices that are easy/difficult, likelihood of practicing the behaviors); includes 2 items from SNF that ask: “Have you shared what you discussed in the EFFECTS parents’ sessions with anyone else?” and if yes, “What is this person or persons’ relationship to you?” (SNF will also be administered as part of outcome evaluation with addition question of: “would you recommend this intervention to family/friends?”
PGSF (refer to outcome forms)	Peer group social support form	Outcome evaluators	Intervention participants	Every 6 months (outcome evaluation)	Dose received (exposure and satisfaction)	A 9-item scale measuring social cohesiveness of peer groups

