
Secondary adjusted analyses will also be conducted using the generalized linear mixed models specified above along with additional outcome-specific predictors (e.g., household wealth or child sex and age) hypothesized to influence the outcome. The large dataset will also allow for additional analyses, such as investigation of potential modifiers and mediators of intervention effects. Potential effect modifiers that might influence the degree of intervention impacts on child nutrition and development outcomes include socioeconomic status, household composition, and intervention process-related factors (e.g., attendance, fidelity, quality of implementation). Potential mediators include maternal and paternal knowledge and caregiving practices for nutrition and ECD, maternal and paternal psychosocial well-being and social support, quality of couples’ relationships, allocation of household resources, and food access.

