**Fig. 4 Fig4:**
[figure not shown]
EFFECTS theory of change

The EFFECTS session topics for the four intervention packages are outlined in detail in Supplementary Table 1. In summary, nutrition-related SBC messages and activities for mothers and fathers address IYCF, dietary diversity, WASH, food access (from local markets and home production), psychosocial well-being, gender equity, intra-household resource allocation (including planning and budgeting for food), partner communication, and household decision-making. Nutrition- and parenting-related SBC messages and activities for mothers and fathers address IYCF, dietary diversity, responsive caregiving and child stimulation (play and communication), praise and positive discipline, WASH, food access (from local markets and home production), psychosocial well-being, gender equity, intra-household resource allocation (including planning and budgeting for food), partner communication, and household decision-making. Each of the above packages was tailored separately for mothers and fathers, resulting in four intervention packages.

Each intervention package includes a trainer’s guide, facilitator’s manual, flipchart, and recipe book. The bundled nutrition and parenting interventions also include a play and communication activity guide adapted from the Care for Child Development intervention developed by the World Health Organization and the United Nations Children’s Fund [35]. Example illustrations of nutrition and parenting content included in the flipcharts are provided in Supplementary Figs. 1 and 2, respectively. Intervention materials are available from the study investigators.

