#### Intervention delivery

Ninety-six peer groups comprising mothers or fathers of children 0–18 months of age (at enrollment) are facilitated by government-supported CHWs (one per peer group), and each group comprises 12 mothers or 12 fathers. Given most villages have two CHWs, one male and one female, the male CHW was assigned to a fathers’ group and the female CHW was assigned to a mothers’ group wherever possible. The CHWs deliver key messages and facilitate problem-solving and skill-building activities to promote nutrition-related or nutrition- and parenting-related behavior change. Group sessions are expected to last approximately 2 h and groups meet bi-weekly for a period of 12 months (24 sessions in total). In the treatment arms that include father groups, approximately one-third of all sessions will be joint sessions where couples participate in the group sessions together. Each group decides where to meet (e.g., in someone’s home, in a community building, outside under a tree). In addition to bi-weekly group sessions, a CHW will make a follow-up home visit to a group participant if the participant misses a group session; the participant scores poorly or provides a low score on (a) participation, (b) recall of messages, and/or (c) satisfaction; the participant shares with the CHW or it is observed by the CHW that s/he is struggling with adopting a new practice or with recalling or understanding key messages; the participant requests a home visit; or the participant shares that a child is ill.

Intervention delivery begins after all baseline data are collected. The 96 CHWs enrolled in the study as EFFECTS peer facilitators will be supervised by a team of eight FS hired for the study (Fig. 3). The FS will be selected based on education levels and relevant experience in community-based programs. Each FS will be assigned to either Musoma or Butiama district and to one of four treatment arms depending in part on the gender of the FS, where male FS will be purposively assigned to the treatment arms with father groups. Thereafter, the FS pairs assigned to the same district and study arm will be assigned (from among the 24 CHWs/peer groups) the 12 CHWs to whom he or she is responsible for providing training and on-going supportive supervision.

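### The egg-and-meat secondary outcome is tested by arm only in households that ate any, a denominator treatment can change; a smaller point is that process factors are listed as effect modifiers

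*Protocol article*

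**What the plan says.** **Egg-and-meat outcome.** Table 1 (Outcomes) lists household allocation of animal source foods as a secondary outcome, measured at baseline, 6 and 12 months. It is the change in the proportion of children aged 6 months or more, mothers and fathers "consuming eggs or meat the previous day given that at least one of the three consumed eggs or meat the previous day". The Analysis plan states an intention-to-treat analysis and fits one model form, with four baseline-to-endline contrasts between arms, for each primary and secondary outcome. No exception is made for this one.

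Under Intervention content, both the nutrition and the bundled packages cover food access and "intra-household resource allocation (including planning and budgeting for food". The Analysis plan itself names food access and allocation of household resources as potential mediators, that is, as things treatment is expected to move.

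**Effect modifiers.** After the main contrasts the Analysis plan says: "The large dataset will also allow for additional analyses, such as investigation of potential modifiers and mediators of intervention effects". The potential modifiers are socioeconomic status, household composition and "intervention process-related factors (e.g., attendance, fidelity, quality of implementation". Under Process evaluation, these data are collected during delivery; that work "will continue throughout implementation in the four EFFECTS intervention arms". Table 3 records attendance at the "Beginning of each bi-weekly peer group session".

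**The concern.** At 6 and 12 months the condition for entering the egg-and-meat denominator is observed after randomisation, and the programme works on it. A household that starts buying eggs because of the sessions enters the denominator in an intervention arm; its counterpart in control does not. The child's own intake can also satisfy the condition, so the numerator can move the denominator. Because entry is decided afresh at each visit, baseline and endline describe different sets of households. The resulting contrast mixes a change in sharing with a change in who is counted, and a programme that gets more children eating these foods could be reported as worsening their share.

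The modifier point is of the same kind but smaller. Attendance, fidelity and quality have no value in control households, and attendance at fathers' groups exists only in the two arms with such groups. Comparing high with low attenders compares self-selected families. Listing these factors beside baseline characteristics invites the same reading for both.

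**Working it through.** **The plan's own figure.** None is given for this outcome. The one fully specified design figure, 0.43 food groups at 80% power, reproduces and is not in dispute. With 12 households per village, 16 villages per arm and ICC 0.1, the design effect is 1 + 11 × 0.1 = 2.1. The standard error is √(2 × 2.1/192) = 0.148 SD, and the detectable difference is 0.414 (normal) or 0.428 (t, 30 df).

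**Egg-and-meat outcome.** All inputs here are assumed.
- p = share of households that would eat eggs or meat anyway (0.40)
- c = share of children eating in those households (0.60)
- g = true gain in that share due to treatment
- d = extra households that eat because of treatment
- n = share of children eating in the extra households

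Take equal baselines and no change in control, so that the difference-in-differences equals the endline difference.

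- Planned (conditional) difference = [p(c + g) + dn]/(p + d) − c = [pg + d(n − c)]/(p + d)
- Difference over all children = pg + dn
- The conditional difference is negative when d(c − n) > pg

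| g | d | n | Planned, points | All children, points |
|---|---|---|---|---|
| 0.05 | 0.20 | 0.30 | (0.02 − 0.06)/0.60 = −6.7 | +8.0 |
| 0.05 | 0.10 | 0.30 | (0.02 − 0.03)/0.50 = −2.0 | +5.0 |
| 0.05 | 0.05 | 0.30 | (0.02 − 0.015)/0.45 = +1.1 | +3.5 |
| 0 | 0.20 | 0.30 | −0.06/0.60 = −10.0 | +6.0 |
| 0 | 0.20 | 0.60 | 0 | +12.0 |
| 0 | 0.10 | 0.90 | +0.03/0.50 = +6.0 | +9.0 |

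In the first row the planned proportion goes from 60% to 53.3% while all-child consumption goes from 24% to 32%. The last three rows have g = 0, so sharing in households that eat anyway is unchanged. The planned contrast still returns −10, 0 or +6 points, depending only on who enters. With n at or above c there is no reversal.

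For fathers: if they eat in 80% of the 40% of households, and a further 20% of households start in which only mother and child eat, the fathers' figure becomes 0.80 × 0.40/0.60 = 53%, although no father eats less.

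The denominator also shrinks. After the 10% loss allowed for, 192 × 0.9 = 173 households per arm remain. If 30% to 60% eat any (assumed), about 52 to 104 contribute, before the age restriction.

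**Attendance.** Borrow 0.43 SD as a true effect that is the same for everyone. Let attendance correlate r with prognosis (assumed) and split it at the median. The mean of a standard normal above its median is 0.798. Against all controls, high attenders show 0.43 + 0.798r and low attenders 0.43 − 0.798r.
- r = 0: 0.43 and 0.43
- r = +0.3: 0.67 and 0.19
- r = +0.5: 0.83 and 0.03
- r = −0.7: −0.13 and 0.99

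Any non-zero r produces apparent modification where there is none. A wrong sign among high attenders needs r below −0.43/0.798 = −0.54; among low attenders it needs r above +0.54.

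**The case against.** The outcome is named as an allocation measure: who eats the food when the household has it. The theory of change keeps allocation apart from access, and an unconditional proportion answers a different question. That stands, and it is why the conditional share should stay in the report. It does not rescue the test: the rows with g = 0 show that the planned contrast is not a clean measure of sharing either.

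The illustration rests wholly on assumed values, and packages that promote child feeding give no reason to expect a low child share in newly eating households. That stands too. A reader might infer that the sign will be reversed; the documents support only that it can be.

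On modifiers, the article describes exploratory work and gives no interaction term, comparison group or test. Process-evaluation aim 2 speaks of associations, so a within-arm dose-response reading is natural. A reader might infer that these results would be presented as trial effects, or that treatment changes attendance. The documents say neither: these factors are defined only under intervention, and the modelling may be in an analysis plan not shown. What remains is that the text lists them as effect modifiers on a par with baseline variables.

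**Conclusion.** The egg-and-meat point holds. One secondary outcome, as defined and tested, conditions on a post-randomisation event that the programmes aim to change, so its contrasts are not protected by randomisation. Size and direction are unknown. Under the assumed values the planned contrast ranges from −10 to +6 points while all-child consumption always rises, by 3.5 to 12 points. Reversal requires newly eating households to share less with the child than existing ones, in sufficient number.

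The modifier point is minor: a matter of labelling in an exploratory sentence, where the likely harm is spurious modification. A reversed sign is possible there, but only with strong selection.

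A reader might extend the concern to the main results. The documents do not support that: dietary diversity and child development are not conditioned on consumption, and their four contrasts stand. The restriction to children aged 6 months or more is harmless in this respect, since treatment does not change age.

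**What to change.** **Egg-and-meat outcome.** Make the randomised comparison the proportions of all children aged 6 months or more, all mothers and all fathers who ate eggs or meat the previous day, together with the proportion of households in which any of the three did. Keep the conditional share as a descriptive allocation measure without arm contrasts. This is a recoding of data already collected. The downside is that the unconditional proportions mix access with allocation; showing the household proportion and the conditional share beside them lets a reader see both. Because it alters a listed secondary outcome, it should be a dated amendment, made before outcomes are compared by arm.

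**Modifiers.** Restrict effect modifiers to baseline variables such as socioeconomic status and household composition. Report attendance, fidelity and quality within the intervention arms under process-evaluation aim 2, labelled as non-randomised associations. This costs only wording.

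Randomised arm should not be used as an instrument for attendance. Under Intervention delivery, "a CHW will make a follow-up home visit to a group participant if the participant misses a group session", and the COVID-19 section says the six sessions still outstanding in March 2020 were delivered at home. Assignment therefore has routes to the outcome other than group attendance, and the exclusion assumption fails.

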### Formative research for intervention design

Prior to the development of intervention packages for the four intervention arms, formative research was conducted over a period of 6 weeks in Musoma Rural and Butiama districts (1) to inform intervention package content by exploring current knowledge, attitudes, practices, relevant socio-cultural and gender norms, and behavior change barriers and enabling factors and by ensuring relevance and acceptability among the community; (2) to test and refine the EFFECTS packages on nutrition and nurturing care; and (3) to adapt and test measures that assess nutrition and nurturing care behaviors that had not been previously used in the local setting. Participants were recruited purposively from two villages in each district to participate in formative research activities. Recruitment criteria included (1) having a child 6–36 months of age, (2) having or being a male partner/father who is resident for at least 10 months of the year in the same home/compound as the female partner and child, and (3) providing informed consent. Additionally, the study team aimed for participant heterogeneity to capture different perspectives and experiences while also maintaining the capability of reaching saturation in participant responses. Therefore, formative research recruitment aimed for representation across maternal age (young vs. older), maternal education level (incomplete primary school vs. completed primary school or higher), distance to market (close to vs. far from), and landholding size (small vs. large, as typical of the region).

The formative research was conducted by local, trained research assistants and consisted of qualitative methods including 12 focus group discussions (FGDs) with mothers; 12 FGDs with fathers; 6 FGDs with both mothers and fathers; 4 pile sort exercises using food cards with mothers; 4 pile sort exercises using food cards with fathers; 12 in-depth interviews (IDIs) with mothers; 12 IDIs with fathers; 4 IDIs with grandmothers; 4 short interviews with older siblings; 4 key informant interviews (KIIs) with CHWs; 4 KIIs with primary healthcare workers; 4 KIIs with community leaders, observations of the caregiving and feeding environment, routines, and resources for each IDI; and 5 village food market assessments. FGDs were structured in such a way that groups of 6–8 participants met over 3 time points, each session covering different content.

The FGDs and IDIs covered the following topics: knowledge, beliefs, attitudes, and practices involving infant and young child feeding (IYCF) and water, sanitation, and hygiene (WASH); individual and joint decision-making within the household; access to food and health resources; preferences and perceptions of local foods; developmental stimulation; parenting practices pertaining to nutrition and development; co-parenting; parenting stressors; and emotional well-being. The KIIs explored perceptions of local barriers and enablers to uptake of nutrition and parenting behaviors, including stimulation, IYCF, WASH, male engagement in childcare and feeding, and local support services. Analysis tables completed by data collectors to synthesize and summarize high-level findings and in-depth content analysis by the study team were used to draft EFFECTS core behaviors, which were revised based on stakeholder input as well as participant feedback on the proposed interventions.

### The EFFECTS nutrition and parenting interventions for mothers and fathers

#### Overview

The EFFECTS social and behavior change (SBC) interventions engage either mothers only or mothers and fathers in a series of bi-weekly peer group sessions (12 participants per group) over 12 months. Depending on which of the four treatment arms to which a sub-village has been randomized (i.e., nutrition only or bundled nutrition and parenting; mothers only or mothers and fathers), the sessions cover gender-specific messaging, activities, and discussions related to IYCF, WASH, food access, parenting (responsive caregiving, play and communication, and managing infant and young child behaviors), management of stress, and shared decision-making and responsibilities between men and women. Our packages were designed to align with the EFFECTS theory of change (described below) and contextualized and tailored based on formative research findings and extensive pilot testing.

For the arms that include both mothers and fathers, mother and father peer groups meet separately but are brought together on at minimum a quarterly basis for a mixed group session focused on communication, decision-making, problem-solving, and consensus building between couples. Employing a community-based peer group design, the 96 peer groups are facilitated by an informal cadre of CHWs (1 CHW per group) who are trained and supervised by eight field supervisors hired and trained specifically for the EFFECTS project (1 field supervisor per 12 CHWs, Fig. 3). Oversight of the implementation is supported by the EFFECTS project manager based at the field office. The details of the four interventions (described below) are reported in accordance with the TIDieR guidelines [34]. In Kiswahili, the EFFECTS project was known as “Malezi Bora.”

